**Abstract**

**Introduction:** HIV/AIDS is the leading cause of mortality among women aged 15 – 44 years. In Africa is there a huge gender disparity in the acquisition of HIV. African women aged 15 – 24 are twice as likely to be infected with HIV than their male counterparts. However, in Cameroon, adolescent girls are five times more likely to be infected with HIV than boys of the same age. Evidence suggests that risks taken during transactional and commercial sexual relationships account for this gender inequality. Recent studies demonstrate that a key driver of a woman’s engagement in risky sexual behaviours is to cope with negative income shocks (e.g., agricultural and climatic shocks, illness or death of family members), suggesting that economic shocks are a substantial piece of the HIV puzzle in Africa. This study is the first to estimate the effectiveness of a formal coping strategy, health insurance, to protect women from economic shocks to prevent STIs and HIV.

**Methods and Analysis**: This study is a stratified cluster randomised controlled superiority trial with two parallel groups. 1,508 unmarried girls and young women engaging in transactional (753) and commercial (755) sex have been recruited onto a baseline study in Yaoundé, Cameroon. Participants are randomised into treatment (receiving health insurance for them and their economic dependents) and control (receiving nothing) groups using participatory randomisation. A target of a 1:1 allocation was stratified by those who engage in commercial or transactional sex. Midline data will be collected at 6 months and 12 months after randomisation.

**Ethics and Dissemination:** This trial has been prospectively registered with the ISRCTN Registry. We obtained ethical approval from Cameroon National Ethics Committee and the UCL ethics committee before data collection. The findings of the trial will be published in peer-reviewed journals irrespective of the final results.

**Trial registration**:

ISRCTN 22516548. Registered on 31 July 2021.

**Funding:**

This project is funded by [name] [name]’s (PI) UKRI Future Leaders Fellowship (round 2, 2020-2024) which is an award by the MRC/ESRC (grant number: MR/S031790/1).

**Keywords**

Randomised controlled trial; health insurance; vulnerable women; STIs/HIV

**Introduction**

**Background and rationale {6a}**

Human immunodeficiency virus (HIV)/ Acquired immune deficiency syndrome (AIDS) is one of the leading causes of mortality globally and is the leading cause among women aged 15 – 44 years. African women aged 15 – 24 are twice as likely to be infected with HIV than their male counterparts (1). In Cameroon, one of the countries with the highest gender disparity in HIV globally, adolescent girls are five times as likely to be infected with HIV than boys of the same age. Sexually transmitted infections (STIs) and HIV not only affect women and their sexual partners, but they are also a special concern during pregnancy and pose serious health risks to unborn children (2). Hence, reducing STI and HIV acquisition in high-risk women can translate into much wider societal benefits and targeted interventions have the potential to provide excellent value for money. There is a growing number of studies showing that risks taken during transactional sex (non-commercial sexual relationships in exchange for material support or other benefits) and commercial sex – in addition to biological susceptibility – are responsible for gender inequalities in HIV/AIDS. However, there is a superficial understanding of the main causes driving risky sexual behaviours of women who engage in those practices in Africa.

Recent studies have shown that women mainly adopt risky sexual behaviours to cope with negative income shocks (e.g., agricultural and climatic shocks, illness or death of family members) and suggest that economic shocks are a substantial piece of the HIV puzzle in Africa (3). Researchers have previously explored the link between poverty and HIV through cash transfers targeting adolescent girls and young women (4). Cash transfers can be an effective way to reduce risky sexual practices among women by increasing their income. However, evidence regarding their effectiveness to prevent HIV is mixed. In Malawi, cash transfers were found to reduce HIV prevalence by 64% (5) while they had limited effect in Kenya (6) and no effect in South Africa (7). The POWER project is based on the assumption that income variability matters more than income level for HIV acquisition, which could explain why cash transfer programs are not always effective. While the literature shows mixed evidence regarding the effect of poverty on HIV prevalence among women (8), there is robust evidence demonstrating that women adopt risky sexual behaviours as a way to cope with economic shocks. Economic shocks are defined as any events that lead to a sudden increase in expenditure level (e.g., illness, COVID-19) or a decrease in income level. In Kenya, it was estimated that an illness of a family member led sex workers to increase unprotected sex by 21 per cent (9). Another study found that each time a village in Africa suffered from a drought, it led to an increase in HIV prevalence in that village by 11 per cent (10). Hence, there is a need to explore whether the effectiveness of some cash transfer programs in reducing HIV acquisition is due to their role in protecting against economic shocks. If so, cash transfers may fail to prevent HIV infection if the amount offered is not large enough to protect against economic shocks or if they are received outside a shock period.

There are several reasons why economic shocks may lead to STIs and HIV acquisition. The main reason lies in the fact that the low access to formal well-paid jobs and productive assets makes women in Africa prone to use commercial and transactional sex as risk-coping strategies. Such strategies may be attractive given that they allow women to raise money quickly and they can earn up to three times more compared to other occupations (11). Relationships developed with men through commercial and transactional sex can also result in other financial or in-kind gifts, which could also help women to cope with economic shocks (12). Women who engage in commercial and transactional sex are incentivised to provide unprotected sex because men are generally willing to pay more for unprotected sex. It is estimated that sex workers can earn 9% more in Kenya and 66% more in India (11) for an unprotected sex act. In addition to unprotected sex, commercial and transactional sex are risky practices because they often lead to multiple, concurrent sexual partners and partners at greater risk of HIV infection (older men and sex workers’ clients). In addition to increasing risky behaviours, economic shocks may also lead to STI and HIV infection if households cut health expenditures concerning STI treatment and HIV prevention services.

Determining whether an economic shock is the missing piece of the HIV puzzle is critical as economic shocks are very common in Africa and these women often lack risk-coping strategies. Economic shocks are a key issue for many African households. At least 60% of African households report large and sudden losses in income every year (13) but only 10% of the poorest households in Africa benefit from social safety net programs to negate income fluctuations (14). Among the shocks experienced by households, health shocks are of particular concern given that they are more frequent, more costly and more concentrated among the poor than other economic shocks (15). If women adopt risky sexual behaviours to cope with negative economic shocks providing women with formal risk-coping strategies could be a very promising approach to preventing HIV. However, no previous study has been designed to specifically answer this research question. Hence, there remain important gaps in understanding.

**Objectives {7}**

**Research Hypothesis**

The main research hypothesis is that women who engage in transactional and commercial sex in Africa use risky sex as a way to cope with economic shocks. Providing health insurance for themselves and their economic dependents is effective to reduce risky sexual behaviours and in turn, prevent STIs and HIV infection among women and girls who engage in commercial and transactional sex.

**Research Objectives**

The general objective of this research is to understand and explore the role of economic shocks (e.g., illness, COVID-19) as a driver of the heightened vulnerability of women to HIV. The identification of the role of economic shocks in STI and HIV acquisition will inform the design of novel public health interventions to tackle STIs and HIV. The RCT aims to estimate the effectiveness of health insurance for high-risk women and their economic dependents as a strategy to prevent STIs and HIV. The POWER project addresses important gaps in the current literature by answering the following research questions:

- What is the role of economic shocks on STIs and HIV?
- How do economic shocks affect STIs and HIV?
- What is the effect of health insurance as a risk-coping strategy to reduce risky sexual behaviours, STIs and HIV?

**Trial design {8}**

This study is a stratified cluster randomised controlled superiority trial with two groups: control and treatment. Private participatory randomisation will be conducted with a target of a 1:1 allocation stratified by the type of risky activity, commercial sex or transactional sex.

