**Intervention description {11a}**

The insurance product, provided by GMC Insurance, covers the participant and up to six of their (nominated) economic dependents and is offered for 12 months. An economic dependent is anyone that depends on the participant financially for health care and can include family members, friends and sex work intermediaries (e.g., pimp). The health insurance product provides free health coverage, there are no out-of-pocket costs, with a cumulative ceiling for each group (the participant and their economic dependents) of 500 000 FCFA (= 638,55 GBP, in 2022 prices) following an illness or an accident and is only valid at the Cité Verte Hospital, Yaoundé, Cameroon. The negotiated ceiling of 500 000 FCFA provides good coverage of health expenses for 12 months in Cameroon. If the sum of 500,000 FCFA has been reached (by the participant and their economic dependents combined), participants must pay for the health expenses themselves. Before the group reaches the 500 000 FCFA limit, the participant will be notified to ensure that they are informed when consuming health care. Costs covered by the insurance product are: consultation fees; pharmaceutical fees; medical fees and; hospitalization fees for non-chronic pathologies. Costs not covered by the insurance product are: chronic diseases (e.g. diabetes, high blood pressure, asthma, sickle cell anaemia, obesity...); maternal health care (prenatal care, delivery, postnatal care); illness resulting from civil or foreign war, civil commotion or riot; injury following a violent quarrel except in cases of self-defence; epidemics declared as such by a competent authority (e.g. COVID-19); cosmetic care; dietary care; weight loss or rejuvenation; sterility or abortion treatment; psychiatric treatment; alcoholism; dialysis; dental care and; ophthalmologic care.

The insurance product was rolled out on the 15^th^ of November 2021 and ended on the 14^th^ of November 2022.

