**Secondary outcome measures**

Secondary outcomes include:

1. Physical health of participants measured using % of participants with good health, % of participants with a chronic illness other than Hepatitis B, the average number of chronic illnesses, % of participants who were sick in the last 30 days, % who sought treatment from a qualified health worker if sick in the last 30 days, % of participants with abnormal levels of Gardnerella vaginalis (GV), Mobiluncus, Candida and streptococcal in the vagina (only at endline)

2. Physical health of economic dependents measured using % of economic dependents with good health, % of economic dependents with a chronic illness, the average number of chronic illnesses per economic dependent, % economic dependents who were sick in the last 30 days, % economic dependent who were sick during sex act with last client, % economic dependents who were sick during sex act with the penultimate client, % of children with good health

3. Beliefs regarding control over own health measured using % who believe that nothing can be done to prevent illness, % who believe that being in good health is a matter of luck

4. Poverty measured using total expenditures, asset index, income from sex work, amount of savings, % who have Informal shock-coping strategies, average amount of transfers received and sent, % who have a debt, amount of the debt, food insecurity

5. Education/training measured using % school dropout, new enrolment in schools, % who are undertaking professional training

6. Other occupation measured using transitions out of sex work, % who have other occupation, share of sex work income in total income

7. Risky sexual behaviours measured using % of condom use with last and penultimate client using a double list experiment and the colourbox method, a newly indirect elicitation method developed by the team members, number of clients per week, type of sex acts performed with last client, self-reported risk preferences with sex (out of 10 scale), % of were pregnant the last 6 months, % who performed both transactional sex and sex work

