**Assignment of interventions: allocation**

**Sequence generation {16a}**

Randomisation is conducted at the individual level using a participatory approach with a target of a 1:1 ratio to treatment or control group stratified by engagement in commercial or transactional sex. Formative research, conducted before randomisation, found that participatory randomisation was the preferred method of randomisation by the target population. Participatory randomisation was deemed fairer and more transparent than computer-based randomisation.

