**Concealment mechanism {16b}**

A protocol has been developed to minimise the opportunity to fix randomisation so participants all receive the treatment. Two balls, one orange (allocating participants to the treatment group) and one white (allocating participants to the control group) are placed in a long black opaque bag. Participants are required to draw one ball out of the bag and cannot see inside. Hence, participant allocation to the treatment and control arm is known by the participants, the enumerators and supervisors at the time of the draw.

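### The protocol labels the trial stratified and cluster randomised but describes a simple individual draw, and it leaves the unit of analysis for dependents' outcomes unstated

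*Protocol*

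**What the plan says.** The design label appears twice. The Abstract states: "This study is a stratified cluster randomised controlled superiority trial with two parallel groups". Trial design {8} repeats it: "This study is a stratified cluster randomised controlled superiority trial with two groups: control and treatment". It adds a 1:1 target, stratified by commercial versus transactional sex.

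The allocation sections describe something else. Sequence generation {16a}: "Randomisation is conducted at the individual level using a participatory approach". Concealment mechanism {16b} puts one ball per arm in an opaque bag, and "Participants are required to draw one ball out of the bag and cannot see inside". Implementation {16c} adds that the bag is first shown to be empty, that the two balls go in while the woman watches, and that she has a single draw.

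Sample size {14} counts individual women (1,508 recruited; 1,147 randomised, 568 to control and 579 to treatment). It gives no number or size of clusters, no intracluster correlation (ICC) and no design effect.

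One draw does reach beyond the woman herself. Under Intervention description {11a} the insurance "covers the participant and up to six of their (nominated) economic dependents". Their health is the second group of secondary outcomes: "Physical health of economic dependents measured using % of economic dependents with good health", among other items. Statistical methods {20a} names ordinary least squares (OLS) for the comparison of arms on primary and secondary outcomes, and says nothing about standard errors or whether dependents enter singly or as a summary per woman.

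**The concern.** The unit of randomisation decides which variance is correct, so a protocol cannot carry two answers. Readers who trust the label will look for a design effect and find none. Readers who trust the allocation sections will wonder which clusters are meant.

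Stratified is also a claim about the allocation. Stratified allocation normally means that something (blocks, a list, a quota) holds the arms close to equal within each stratum. A fresh two-ball bag for every woman makes each allocation an independent 50:50 event, so the draw has no memory of the stratum.

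The one place where a shared allocation does group people is a woman and her dependents, and there the protocol gives no direction. An analyst who applied the named model to a file with one row per dependent and default standard errors would understate the uncertainty.

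**Working it through.** **1. Is there a cluster?** The candidates are the host organisations, the peer-referral chains and the woman with her dependents. The first two are groups within the sample, but the protocol does not allocate them as groups. Each woman draws for herself. For women's own outcomes the cluster size is therefore m = 1, and the design effect 1 + (m − 1) × ICC equals 1 whatever the ICC.

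**2. Which design do the stated power figures fit?** Inputs from Sample size {14}: 20% versus 14% for any STI, 80% power, 5% significance (taken as two-sided), 568 and 579 randomised. The check is a two-proportion normal test with pooled variance under the null and no design effect.

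- Required n per arm = [1.96 × √(2 × 0.17 × 0.83) + 0.8416 × √(0.20 × 0.80 + 0.14 × 0.86)]² / 0.06² = 615, or 1,230 in total.
- Power at 568/579 is 77.3%; at 754 per arm (1,508) it is 87.4%. Neither reproduces 80% exactly.
- Minimum detectable differences at 80% power, in percentage points:

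| | Stated | 568/579 | 600/600 |
|---|---|---|---|
| Any STI, all women | 6 | 6.2 | 6.07 |
| Any STI, one stratum (half the sample) | 8.3 | 8.5 | 8.33 |
| HIV (from 4%) | 2.6 | 2.66 | 2.62 |

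All three stated figures match about 1,200 individually randomised women with no design effect.

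**3. What would a literal cluster reading imply?** With assumed design effects of 1.1, 1.25, 1.5 and 2.0, power at 568/579 would fall from 77.3% to 73.3%, 67.8%, 59.9% and 48.2%. Nothing in the protocol points to such an inflation; step 2 points to a wrong word.

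**4. How far could strata drift under a simple draw?** Stratum sizes among the randomised are not given. Assuming an even split, each has 1,147 / 2 ≈ 573 women. The standard deviation of the treated share is 0.5 / √573.5 = 2.1 points, so 95% of draws lie within about ±4.1 points of 50%. The overall split is 5.5 women from even (579 − 573.5), against a standard deviation of √1,147 / 2 = 16.9. Chance imbalance is likely to be modest, but the draw does not limit it.

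**5. Dependents analysed one row each with independent errors.** True size of a nominal 5% test = 2 × [1 − Φ(1.96 / √DE)], with DE = 1 + (m − 1) × ICC and m dependents per woman. Eligibility requires at least one dependent and the insurance caps them at six. The mean number and the ICC are not in the protocol, so both are assumed.

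| m | ICC 0.05 | ICC 0.1 | ICC 0.2 |
|---|---|---|---|
| 1, or one summary per woman | 5.0% | 5.0% | 5.0% |
| 3 | 6.2% | 7.4% | 9.8% |
| 4 | 6.8% | 8.6% | 12.1% |
| 6 | 8.0% | 11.0% | 16.6% |

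Worked case: m = 6, ICC 0.2 gives DE = 1 + 5 × 0.2 = 2.0, 1.96 / √2 = 1.386, and a size of 16.6%.

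**The case against.** The strongest reply is that this is a wording slip with no effect on the primary analysis. For women's own outcomes, including STI and HIV, that is right.

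A reader might infer that the plan analyses dependents with uncorrected OLS. The text does not say so. OLS is compatible with cluster-robust standard errors and with one proportion per woman, the outcomes are worded as percentages and averages, and the variance estimator for a secondary outcome is commonly left to the statistical analysis plan, which is not at hand. The inflation in step 5 is therefore conditional. What stands is narrower: a protocol that uses the word cluster should say where clustering exists, and here it does not.

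A reader might also infer that, without balanced strata, the model must adjust for sex-work type. It need not. Under simple 1:1 individual randomisation the unadjusted comparison is unbiased and its type I error is correct; adjustment can only help precision. The protocol also already plans separate analyses by sex-work type and adjustment for baseline differences.

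Nor are dependents' outcomes the only correlated data. Midline and endline visits, the SMS series and the items on the last and penultimate client are repeated within a woman.

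**Conclusion.** The contradiction is established on the face of the protocol. The Abstract and Trial design {8} claim cluster randomisation, which the allocation sections and the sample size exclude. The claimed stratification is not something the described draw can deliver.

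The consequence is limited. Correcting the label leaves every participant-level figure as it is. It would be wrong to conclude that the STI and HIV power statement omits a design effect, because none is due. The shortfall from 80% at the randomised numbers (77.3%) is a separate matter and does not arise from clustering.

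For dependents' outcomes, the exposure runs from none (one dependent, or one summary per woman) through about 6% (three per woman, ICC 0.05) to about 17% (six per woman, ICC 0.2). It arises only under row-level analysis with independent errors. The numbers per woman and the ICCs are assumptions, and a larger ICC would go further (21.5% at six per woman and ICC 0.3). It concerns one of 16 groups of secondary outcomes. The point merits correction but does not threaten the primary inference.

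**What to change.** - In the Abstract, Trial design {8} and Sequence generation {16a}, describe the trial as individually randomised, 1:1, by simple participatory draw, and delete cluster.
- In the same places, say that the draw does not balance sex-work type. In Statistical methods {20a}, name it as a prespecified covariate in the pooled OLS model, for precision and not as a condition of validity.
- In Statistical methods {20a}, or in the statistical analysis plan with a cross-reference, state that dependents' outcomes use standard errors clustered on the participant or are reduced to one summary per participant.

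The cost is a few sentences and one option in the Stata command. Sex-work type is already collected, and no sample-size figure or trial procedure changes. The price is somewhat wider intervals for dependents' outcomes than a row-level analysis with independent errors would show.

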**Methods: Participants, interventions and outcomes**

**Study setting {9}**

The trial is being conducted in Yaoundé, Cameroon. Cameroon was chosen because it has one of the highest gender disparity in HIV globally, adolescent girls aged 15–19 are five times more likely to be infected with HIV than their male counterparts [2% versus 0.4%] (16).

The implementing partner is John Hopkins Cameroon Program (JHCP), an NGO experienced in conducting research for John Hopkins University. Recruitment of participants using respondent-driven sampling (RDS) is hosted by two partner Community-based organisations (CBOs), Horizon Femmes (HF) and RENATA. HF and RENATA were chosen because of their extensive experience and excellent ongoing work in STI and HIV prevention with the target population. Both organisations were recommended by the implementing partner JHCP.

All women and girls engaging in commercial and transactional sex who have received a recruitment coupon and meet the eligibility criteria can participate. Recruitment of participants into the study began in June 2021. The randomisation of participants began in October 2021.

After negotiations with several health insurance and care providers in Cameroon and on the advice of local partners (JHCP, HF and RENATA), GMC assurances and Cité Verte Hospital were the chosen health insurance and healthcare providers. GMC assurances was chosen as they offered the best value insurance package. The choice of hospital was based on the quality of care, availability of medication on site and the positive culture and experience in providing care to stigmatised and vulnerable groups.

